### Blinding

Therapists responsible for conducting assessments will be blinded to group allocation. The persons that will score the assessments are not the same as those that conduct the assessments or the intervention. They will be blind to group allocation by analysing coded videos. Also, the person responsible for data and statistics analysis will be blind. For methodological reasons and due to the nature of the interventions, it will not be possible to blind the therapists that will perform the interventions.

The allocation will not be disclosed to the patient/parents, the therapist from the other group, the evaluators and other research participants.

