### Outcomes measures

After acceptance to participate in the study and before randomization, the basic measures and anthropometric data, general health data and socioeconomic aspects of each family / infant will be collected (T0).

All assessments will be conducted online. The study will have at least 4 evaluators. All evaluators are trained physiotherapists, with experience in the field of pediatrics and in the scales applied. Evaluators will be trained on the application, scoring and interpretation of all scales. For all outcomes, the inter-examiner and intra-examiner reliability calculation will be calculated using the Intraclass Correlation Coefficient (ICC). For the analysis of the ICC, the classification recommended by Weir (2005) will be considered: null: 0.00; weak: 0.01 to 0.30; regular: 0.31 to 0.60; strong: 0.61 to 0.90 and excellent: 0.91 to 0.99; and full = 1.00.

The primary outcomes will be motor capacity that will be assessed by the Infant Motor Profile (IMP) and Alberta Infant Motor Scale (AIMS). The secondary outcomes will be: a) participation assessed by the Young Children’s Participation and Environment Measure (YC-PEM), b) the parent-infant interaction assessed by the Parent-Child Early Relational Assessment (PCERA), c) the environmental changes assessed by the Affordances in the Home Environment for Motor Development (AHEMD). The assessment instruments according to the International Classification of Functioning, Disability and Health (ICF) biopsychosocial scheme are shown in Fig. 3.

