Assessments will take place in four ways, depending on the instrument in question:SPONTANEOUS FILMING: video recording of the infant by parents, on scales that do not require simultaneous instruction. Parents will receive an online document, with all instructions related to the positioning of the infant, in which case the filming should take place, use of toys or stimuli. The PCERA instrument will be applied in this way.FILMING WITH ASSISTANCE: parents will be asked to take part in a video-based telehealth appointment with the evaluator. In the video interaction, the researcher will guide the parents in relation to how to carry out the activities, which positions and stimuli are recommended according to the components of the scale. Parents will apply activities on the infant simultaneously to the video transmission, so that the researcher can correct and guide caregivers in real time. The video stream will be recorded for later scoring. The following instruments will be evaluated in this way: AIMS and IMP.ONLINE QUESTIONNAIRE: the assessment scales that can be self-completed by caregivers will be transformed into online questionnaires. The AHEMD instrument will be evaluated in this way.PHONE CALL: assessments that must be answered by the caregivers but applied by the therapist. The YC-PEM instrument will be evaluated in this way.

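### Both primary outcomes are scored from a recorded live call with the caregiver who delivers the programme; coding the videos does not hide what is said, so scorer blinding at T1 and T2 is not secured.

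*Protocol article*

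**What the plan says.** Under Outcomes measures, motor capacity is the primary outcome, measured by IMP and AIMS at T0, T1 (after 5 weeks) and T2 (after the intervention). The paragraph on filming with assistance describes the capture: "parents will be asked to take part in a video-based telehealth appointment with the evaluator". The caregiver handles the infant during the transmission, "so that the researcher can correct and guide caregivers in real time". Then: "The video stream will be recorded for later scoring". The paragraph closes: "The following instruments will be evaluated in this way: AIMS and IMP".

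The Blinding section separates the roles: "The persons that will score the assessments are not the same as those that conduct the assessments or the intervention". It gives the means by which scorers are kept blind: "They will be blind to group allocation by analysing coded videos". It also states: "The allocation will not be disclosed to the patient/parents, the therapist from the other group, the evaluators and other research participants". It says that the therapists who deliver the interventions cannot be blinded.

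Under Participants, the caregiver is the person who applies the home intervention. Table 1 gives the STEP arm only: goals set with the therapist on the GAS scale, a participation booklet, and an illustrated manual on interaction. Both arms receive a booklet of functional activities, advice on a proper environment with appropriate toys, weekly meetings and the same motor dose.

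**The concern.** The scored material is not a silent clip of an infant. It is the record of a two-way conversation with the adult who, by T1 or T2, has spent 5 or 10 weeks delivering one of the two programmes. A passing remark about the goals agreed with the therapist, or about the participation or interaction material, points to STEP whether or not the caregiver knows the name of the group. Coding the file does not remove that remark.

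Blinded scoring carries much of the weight in the motor comparison, because the intervention therapists are unblinded and the caregivers know what they have been asked to do. The stated hypothesis is directional (higher motor scores with STEP). A scorer who can tell the arm has room to lean that way, most of all on IMP, and the report would still describe the scoring as blind.

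**Working it through.** **The text, step by step**

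1. Which outcomes: AIMS and IMP, both primary (Outcomes measures, Table 2).
2. What is scored: the recorded stream of the live appointment (filming with assistance).
3. Who is on the recording: the evaluator and the caregiver, in real-time exchange.
4. What that caregiver knows: the content of the assigned programme (Participants, Table 1).
5. When it matters: T1 and T2. T0 precedes randomization and is unaffected. The Statistical analysis section makes the end-of-intervention comparison the main one, so T2 matters most.
6. What protects the scorer: a separate person, non-disclosure of allocation to parents, and coded videos. Only the last concerns the recording itself, and it acts on the label.

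**Which remarks would identify the arm (Table 1)**

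| Remark | Control | STEP | Identifies the arm? |
|---|---|---|---|
| GAS goals set with the therapist | no | yes | yes |
| Participation booklet | no | yes | yes |
| Interaction manual | no | yes | yes |
| Activity booklet | yes | yes | no |
| Appropriate toys, in general terms | yes | yes | no |
| Weekly meeting, daily motor tasks | yes | yes | no |

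The route is narrow but real: three kinds of remark out of the many a caregiver might make.

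**Size, by assumption only**

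The documents give no figure for this risk, so there is no plan figure to reproduce. Assume that a share *s* of STEP recordings reveals the arm, that scores on those recordings rise by *k* SD, and that control scores do not move. Then bias = *s* × *k*.

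- Low: 0.2 × 0.2 = 0.04 SD
- High: 0.4 × 0.5 = 0.20 SD

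For the planned t-test with no true effect and *n* = 30 per arm (Sample size section), the statistic follows a noncentral t with 2 × 30 − 2 = 58 degrees of freedom and noncentrality bias × √(*n*/2) = bias × √15. The two-sided 5% critical value is 2.002.

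- Bias 0.04: noncentrality 0.155; rejection 3.53% (favouring STEP) + 1.73% (favouring control) = 5.3%
- Bias 0.10: noncentrality 0.387; rejection 5.72% + 0.96% = 6.7%
- Bias 0.20: noncentrality 0.775; rejection 11.54% + 0.32% = 11.9%

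With 26 per arm (the 52 before the dropout allowance), a bias of 0.20 SD gives 10.9%.

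**The case against.** The strongest case against is that this argues from silence. The article does not say that sound is kept, what coding covers, or what evaluators tell caregivers; such details may sit in an assessment manual. The stated scheme also has several layers: separate scorers, blinded assessors, parents not told their allocation, therapists kept apart, and a blinded analyst. This stands in part. It rules out saying that blinding is broken. It does not remove the point, because the article names a mechanism and says that scorers are blind by it, and its own account of the recordings shows that this mechanism alone does not deliver that.

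A second objection is that much of what caregivers say is common to both arms. That is right, and the point is limited accordingly. The Delivery and fidelity section even has therapists in both groups trained in setting therapy goals, so loose talk of goals is a weaker clue than a mention of GAS goals or the two STEP-only documents.

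Third, AIMS consists of 58 items scored 0 or 1, and the team reports inter-rater reliability above 0.9 for AIMS and above 0.8 for IMP. The item format does make AIMS less open to a shift. Reliability does not exclude bias, since two raters who hear the same remark can move together.

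Two stronger readings are tempting. A reader might infer that caregivers cannot be masked at all; the Blinding section says this only of the intervention therapists. A reader might also set the assumed bias against the planned effect of 0.23 and call it 17% to 87% of that effect (0.04/0.23 to 0.20/0.23). That requires 0.23 to be a standardised mean difference, for which a t-test at 90% power would need 398 per arm. The stated 52 reproduces instead with 0.23 as Cohen's f in a repeated-measures group-by-time interaction (two measurements, correlation 0.5 assumed; power 0.902). On the usual conversion d = 2f = 0.46 the share would be about 9% to 43%. The article does not name the test, so neither share is relied on here.

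**Conclusion.** The point holds in a limited form. As written, the plan leaves a route by which scorers of both primary outcomes could learn the arm at T1 and T2, and the one stated safeguard on the recordings does not close it. Blinding is unsecured on the text, not shown to have failed. IMP is more exposed than AIMS.

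The size is unknown. The range of 5.3% to 11.9% for the false-positive rate rests wholly on the assumed 20% to 40% of STEP recordings revealing the arm and the assumed shift of 0.2 to 0.5 SD in those; its lower end is negligible. The case for acting is that a cheap measure protects the main comparison, not that a large bias has been demonstrated. If sound is already removed before scoring, a sentence saying so settles the matter.

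**What to change.** State in the Blinding section, and in the paragraph on filming with assistance, that AIMS and IMP are scored from recordings with the sound removed. Both rate visible posture and movement. Have the evaluator open each T1 and T2 session with a fixed sentence asking the caregiver not to mention goals, booklets or activities. PCERA rates interaction, where voice matters, and keeps its sound.

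The cost is muting each file when it is coded, plus one scripted sentence per session. The change can be applied to any recording not yet scored. The downside is small: the scorer loses any spoken context for an infant's behaviour.

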### Statistical analysis

The statistical analysis used will follow the standard principles for randomized controlled studies. The SPSS 17 software will be used for data analysis. The analysis of main interest of the study is the comparison between the groups at the end of the intervention. Data from participants who drop out of the study will be stored and all children entered initially (with assessment of the baseline measures) will be included in the intention-to-treat analysis, with a significance level of *p* < 0.05.

To test the difference between the two groups in maternal and infant characteristics (birth weight, gestational age, sex and corrected age) and in baseline measures (AIMS, IMP, YC--PEM, PCERA and AHEMD-IS) will be used the t test for parametric data and the Mann-Whitney test for non-parametric data. In order to verify the effect of the experimental intervention versus the conventional guidelines for primary and secondary outcomes, the t-test and the Mann-Whitney test will be used. The effect size will be calculated using Cohen’s d.

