### Participants

Infants from 3 to 9 months corrected age, of both sexes, and with moderate to high risk for developmental delay will be included in the study. Infants who present at least two of the following biological risks for developmental delay will be included: a) prematurity (< 33 weeks of gestational age); b) low weight; c) asphyxia (Apgar score from 0 to 3 for more than 5 min and / or neurological manifestations in the neonate such as seizures, coma or hypotonia); d) the need for cardiorespiratory resuscitation or the use of oxygen therapy; e) prolonged length of stay in the Intensive Care Unit (more than 7 days); f) Abnormal General Movements, assessed by General Movement Assessment (GMA). Infants with the absent fidgety or abnormal fidgety general movements will be included in the study [27]. The infant will be filmed for 5 min, in the supine position, wearing only a diaper. For infants assessed before completing 3 months of corrected age, writhing movements will be assessed. Infants who have cramped-synchronized movements or poor repertoire will be included [28].

Infants will be excluded from the study if they have: a) primary diseases already diagnosed and congenital diseases; b) suspected or confirmed blindness or deafness; c) unstable health status, such as severe respiratory illnesses and frequent or uncontrolled epilepsy.

The caregivers of the infants will also be participants of the study, since they will apply the home intervention. The caregiver that will be responsible for the intervention at home will be the person that is available to apply the intervention in the specified time and that spends most time with the infant. Thus, participants will also be excluded if they have caregivers/parents with the following characteristics: a) cognitive or motor impairments that prevent the understanding or performance of activities administered at home; b) not fluent in Brazilian Portuguese.

Infants may discontinue their participation in the study in the following situations: a) parental withdrawal; b) not performing intervention procedures in the first 7 days of treatment; c) inability to receive online monitoring and evaluation; d) do not perform at least 75% of the planned therapy sessions at home (controlled at the end of the intervention) or do not perform the interventions for two consecutive weeks (controlled weekly).

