**Fig. 3 Fig3:**
[figure not shown]
Assessment instruments organized in the CIF scheme. Legend: GMA: General Movements Assessment; PCERA - Parent-Child Early Relational Assessment; IMP - Infant Motor Profile; YC-PEM - Young Children’s Participation and Environment Measure; AIMS - Alberta Infant Motor Scale; AHEMD - Affordances in the Home Environment for Motor Development

All these measures will be applied before the intervention (T0). After 5 weeks of intervention (T1) both groups will be evaluated by the AIMS and IMP, to verify the evolution and possibly redirect the activities. After completion of the intervention (T2) all outcomes will be applied again. More details about the outcomes and their applications are found in Table 2.

**Table 2 Tab2:** Study outcomes

Scale	Outcome	Assessment method	Description	Statistical analysis	Timepoint
Alberta Infant Motor Scale	Primary	Filming with assistance	The scale assesses the motor skills of infants from 0 to 18 months [31]. It is validated for the Brazilian population [32]. Studies demonstrate that home video evaluation of this scale, performed by parents, has validity [33, 34]. We performed the inter-rater reliability analysis with high-risk infants and found values above 0.9, indicating high reliability. The scale consists of 58 items, in which the child is evaluated in the four postures: prone, supine, sitting and standing. In the application of the scale, when the infant is able to perform a certain item, a score of 1 is generated and when he is unable to perform it, a score of 0 is obtained, totaling up to 58 points. The sum of all scales defines the gross AIMS score. This score is transformed into a percentile that represents the child’s motor development [31, 32].	AIMS percentiles	T0, T1 and T2

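### The intention-to-treat set is every child with baseline data, but the only effect tests named, run on observed T2 scores, omit children without T2, use neither T0 nor T1, and cannot carry the promised therapy-dose covariate

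*Protocol article*

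**What the plan says.** All places are in the protocol article.

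- **Analysis set** (Statistical analysis): "all children entered initially (with assessment of the baseline measures) will be included in the intention-to-treat analysis". The set is therefore defined by having T0 data.
- **Dropouts** (same section): "Data from participants who drop out of the study will be stored". Nothing further is said about how they enter a test.
- **Main comparison** (same section): "The analysis of main interest of the study is the comparison between the groups at the end of the intervention".
- **Effect tests** (same section): "for primary and secondary outcomes, the t-test and the Mann-Whitney test will be used".
- **T1** (Outcomes measures): "both groups will be evaluated by the AIMS and IMP, to verify the evolution and possibly redirect the activities". Table 2 gives T0, T1 and T2 for AIMS and IMP, and only T0 and T2 for the three secondary instruments.
- **Planned loss** (Sample size): 52 children are needed, 15% are added, and 30 per group are randomised.
- **Discontinuation** (Participants): infants may leave for several reasons, including that they "do not perform at least 75% of the planned therapy sessions at home", which is checked at the end of the intervention.
- **Covariate** (Intervention): the total dose of therapies is to be added as a covariate in the analysis.

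**The concern.** The analysis set needs only a T0 assessment, while the named tests need a T2 score. A two-sample test on observed T2 values drops every child without one, so what is called intention-to-treat would in practice be a complete-case comparison. Storing a dropout's data does not bring that child into the test.

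The same tests have two further limits. They ignore the child's own baseline, which is usually the strongest predictor of a motor score ten weeks later. They also take no covariate, although one is promised. The misfit therefore lies between things the article itself fixes: its analysis set, its tests and its covariate.

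At stake are precision and, if the children lost differ between arms, the size of the estimated effect. Unequal loss is plausible but not documented: STEP parents are asked to do more, and two of the discontinuation criteria (nothing done in the first 7 days, two consecutive weeks missed) turn on parents not carrying out the intervention.

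**Working it through.** **1. The plan's own figures.** The article does not say which effect size 0.23 is. Read as f for a group-by-time interaction with 2 groups, 2 measurements and an assumed correlation of 0.5, the noncentrality is f² × N × 2/(1 − 0.5) = 0.0529 × 52 × 4 = 11.00 on 1 and 50 degrees of freedom. Power is 0.902, so 52 is reproduced. Then 52 × 1.15 = 59.8, giving 60. A two-sample t-test with d = 0.23 would need 796 in total, so the number appears to come from a repeated-measures calculation and not from the test named.

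**2. Children without T2.** 60 − 52 = 8 (13.3%). If the loss is truly 15%, 0.15 × 60 = 9, leaving 51. On the basis in step 1, power is 0.939 with 60, 0.902 with 52 and 0.896 with 51. The issue is therefore not mainly the power lost with the dropouts.

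**3. Precision.** Assumptions, none given in the article: 30 per arm, SD 1 at each visit, correlations T0–T1 0.70, T0–T2 0.60, T1–T2 0.75, and random 15% loss after T1, so 25.5 per arm at T2. Large-sample standard errors of the T2 contrast:

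- t-test on observed T2: √(2/25.5) = 0.280.
- Same children, adjusted for T0: √(2 × (1 − 0.60²)/25.5) = √(1.28/25.5) = 0.224.
- Likelihood with T0 and T1. The slope of T2 on T1 given T0 is (0.75 − 0.70 × 0.60)/(1 − 0.70²) = 0.33/0.51 = 0.647. The slope on T0 is (0.60 − 0.70 × 0.75)/0.51 = 0.147. R² = 0.647 × 0.75 + 0.147 × 0.60 = 0.574. The standard error is √[2 × (0.426/25.5 + 0.647² × 0.51/30)] = √[2 × (0.0167 + 0.0071)] = 0.218.

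Simulation at this sample size gives 0.284, 0.227 and 0.221. Of the total fall of 0.063, baseline adjustment accounts for 0.284 − 0.227 = 0.057, or about nine-tenths. Adding T1 contributes 0.006.

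**4. Bias.** Suppose a fraction p of an arm is lost from the low end of T1 plus noise (noise SD 0.5, so this score correlates 1/√1.25 = 0.894 with T1). The mean T2 of those who remain shifts up by ρ × 0.894 × φ(z_p)/(1 − p), where ρ is the T1–T2 correlation and z_p the normal quantile at p. The last factor is 0.109, 0.195, 0.350 and 0.424 at 5%, 10%, 20% and 25% loss. With ρ = 0.7:

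- 5% against 25%: 0.7 × 0.894 × (0.424 − 0.109) = 0.197 SD.
- 10% against 20%: 0.7 × 0.894 × (0.350 − 0.195) = 0.097 SD.
- Equal loss in both arms: 0.

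Simulation agrees (0.197, 0.093, about 0). For ρ from 0.5 to 0.8 the simulated ranges are 0.14 to 0.22 SD and 0.07 to 0.11 SD for the two unequal cases. An estimator that uses T1 brings the bias to about zero in every case.

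A different scenario uses a true effect of 0.46 SD and ties loss to low T1 in the STEP arm only. The complete-case estimate is then about 0.57 to 0.60, depending on how the loss is generated. If the same dependence acts in both arms there is no bias.

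**The case against.** The strongest reply is that the two sentences can coexist. A t-test or Mann-Whitney test can be run on imputed T2 values, and an imputation rule may sit in the full protocol or analysis plan, which is not shown. That stands: the absence of such a rule from an article is not itself a fault. What remains is that the tests named do not by themselves deliver the stated analysis set, and that even with imputation they neither use the baseline score nor take a covariate.

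Four stronger readings are tempting, and the documents do not support them.

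- **That the T1 data are wasted.** T1 has a stated purpose, monitoring progress and possibly redirecting activities. The accurate statement is that no named analysis uses T1 to inform a missing T2 value. T1 also exists only for AIMS and IMP.
- **That the 75% adherence rule removes children from T2.** It is checked at the end of the intervention, when T2 is due, and the article does not say T2 is skipped. It also says infants may discontinue, not that they must.
- **That the effect will be overestimated by about 30%.** That figure (0.60 against 0.46) needs poor T1 performers to be lost in the STEP arm alone. Nothing in the article says loss is arm-specific.
- **That the gain in precision measures the cost of losing dropouts.** Step 3 shows it is nearly all ordinary baseline adjustment.

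T1 also has limits as a remedy. A child who leaves in the first week has no T1, and no model based on T0 and T1 removes bias if loss depends on the unseen T2 score itself.

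**Conclusion.** The point holds in this form: the analysis set is defined by T0, but the named tests, applied to observed T2 scores, omit about 8 or 9 of 60 children at the planned loss, ignore T0 and T1, and cannot carry the promised covariate. It should be changed, but it is not a fatal flaw.

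Under the assumed correlations and random 15% loss, the standard error falls from about 0.28 to 0.22 SD, and adjusting for T0 alone already gives about 0.227. Complete-case bias is conditional. It is about zero if informative loss is equal in the two arms, and roughly 0.1 SD at 10% against 20% loss, with larger values only under more unequal loss. The correlations, the effect of 0.46 SD and the loss mechanisms are all assumptions, so these figures show scale and are not predictions.

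**What to change.** **IMP and AIMS.** Take the primary T2 contrast from a likelihood-based repeated-measures model with T0, T1 and T2 as responses, a common T0 mean, arm-by-visit terms and an unstructured covariance. Multiple imputation using T0 and T1, followed by a baseline-adjusted comparison, is an acceptable alternative. Either makes the intention-to-treat sentence true and can carry a covariate. Whether to adjust for therapy received after randomisation is a separate question.

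**YC-PEM, PCERA and AHEMD.** Use a comparison adjusted for T0. Say plainly that a child with T0 only adds almost nothing to the T2 contrast for these outcomes.

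**AIMS percentiles.** These are bounded, so keep a rank-based sensitivity analysis.

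**Follow-up.** State whether children who meet a discontinuation criterion listed under Participants are still assessed at T2.

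**Minimum.** If the two-sample tests are kept, state how children without T2 enter them, or call the result a complete-case analysis.

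**Cost.** This is a change of wording: the assessments used are already scheduled. The price is a more complex model that relies on normal theory, which is why the rank-based check is kept.

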**Methods:**

Randomized controlled trial. Infants at risk, with 3 to 9 months corrected age, will be included, and randomized into two groups: control group (conventional guidelines) and experimental group (task, environment and participation in context-specific home program). Infants will be assessed for motor capacity (Infant Motor Profile and Alberta Infant Motor Scale); participation (Young Children’s Participation and Environment Measure) and environment factors (Parent-Child Early Relational Assessment; Affordances in the Home Environment for Motor Development). The intervention period will be 10 weeks, and evaluations will be carried out before and after that period. All the assessment and intervention procedures will be carried out online, with instructions to parents for home therapy. The statistical analysis will be guided according to the distribution of the data, and a significance level of 5% will be adopted. All ethical approvals were obtained by the Ethics Committee of the University of São Carlos (Case number 31256620.5.0000.5504). The protocol will follow the SPIRIT statement. Findings will be disseminated in peer-reviewed publications and presented at national and international conferences.

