### Sample size

The study will have a non-probabilistic convenience sample. The sample calculation was performed a priori using the G*Power software. Sample size was determined based on the data obtained in the study by Hielkema [25], from the total score of the Infant Motor Profile (IMP) scale. An effect size of 0.23, statistical power of the test of 90% and statistical significance of 5% were considered. The sample calculation resulted in 52 participants. To guarantee a sufficient number of participants, the inclusion of 15% more participants was established in order to meet a possible dropout rate. Thus, the allocation of 30 participants in each group was determined.

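### The end-of-intervention comparison uses a two-sample test with no adjustment for T0 score or, chiefly for the IMP, for age, so precision is lost and chance baseline imbalance stays uncorrected

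*Protocol article*

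**What the plan says.** All references are to the protocol article.

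- **Main contrast (Statistical analysis).** "The analysis of main interest of the study is the comparison between the groups at the end of the intervention".
- **Test (Statistical analysis).** To assess the experimental intervention against conventional guidelines, "for primary and secondary outcomes, the t-test and the Mann-Whitney test will be used". Effect size is to be given as Cohen's d. The abstract adds: "The statistical analysis will be guided according to the distribution of the data". No rule for choosing between the two tests is given.
- **Use of baseline and age (Statistical analysis).** Corrected age, other infant and maternal characteristics and all baseline scales are compared between arms by the same two tests. No other use is described.
- **Data available (Outcomes measures, Table 2).** All outcome scales are applied at T0 and T2; the IMP and AIMS are also applied at T1. The AIMS is analysed as percentiles. The IMP is analysed as a weighted average score, with no age standardisation described.
- **Population (Participants).** "Infants from 3 to 9 months corrected age, of both sexes".
- **Allocation (Randomization).** 1:1 in blocks of 6; no stratification by age or baseline is mentioned.
- **Covariate (Intervention).** The total dose of therapies is to enter the statistical analysis as a covariate.
- **Sizing (Sample size).** The basis is the IMP total score in a cited study. The assumptions read: "An effect size of 0.23, statistical power of the test of 90% and statistical significance of 5% were considered". The outcome is 52 evaluable infants, raised by 15% to 30 per arm.

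**The concern.** A motor score at T2 depends partly on where the infant stood at T0 and, if the score is not age-standardised, on how old the infant is. Entry at 3 to 9 months plus 10 weeks (about 2.3 months) puts ages at T2 between roughly 5.3 and 11.3 months. A two-sample test on T2 scores leaves the variation explained by T0 in the error term. For the IMP it leaves age variation there as well. Any chance difference between arms at T0 also carries through to the estimated effect. The baseline significance tests correct neither problem.

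The plan is also not consistent about covariates. Intervention promises one, but neither test named under Statistical analysis can carry a covariate. The one promised is measured after randomisation, while the pre-randomisation variables most likely to predict the outcome are left out.

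What is at stake is efficiency and protection against an unlucky allocation in a trial of 60 infants.

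**Working it through.** **Inputs from the article.** Effect size 0.23 (metric not named), power 90%, significance 5% (sidedness not stated, taken as two-sided), 52 evaluable (26 per arm), 60 allocated.

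**Inputs assumed.** T0-T2 correlation r from 0.3 to 0.8, because none is given. For power, d = 0.46, with other values shown. The value 0.46 comes from reading 0.23 as Cohen's f, since d = 2f with two equal groups.

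**1. Reproducing the plan's 52.**
- Two-sample t-test, d = 0.23: 399 per arm (798 in total) two-sided; 325 per arm one-sided.
- Two-sample t-test, d = 0.46: 101 per arm (202 in total) two-sided; 82 per arm one-sided.
- Repeated-measures ANOVA, group-by-time interaction, two groups, two time points, f = 0.23, assumed correlation 0.5: noncentrality f² × N × m / (1 − r) = 0.0529 × 52 × 2 / 0.5 = 11.0 on (1, 50) df. Power is 0.902 at N = 52 and 0.890 at N = 50, so N = 52.
- The within-subject time test gives the same 52. The interaction with three time points gives 42. The between-group repeated-measures test with two time points gives 152.
- 52 × 1.15 = 59.8, hence 60.

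The only variants tried that return 52 use T0. This suggests, but does not prove, that the sizing relied on baseline information that the named tests do not use.

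**2. Variance left after adjusting for T0.** ANCOVA leaves 1 − r² of the T2 variance. The unadjusted sample of equal precision is 52 / (1 − r²).

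| r (assumed) | variance left | equivalent unadjusted N |
|---|---|---|
| 0.3 | 91% | 57 |
| 0.5 | 75% | 69 |
| 0.7 | 51% | 102 |
| 0.8 | 36% | 144 |

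**3. Power, 26 per arm, two-sided 5%.** Noncentral t with noncentrality d × √(26/2) / √(1 − r²); 50 df unadjusted, 49 df adjusted. For d = 0.46 the unadjusted value is 0.46 × 3.606 = 1.659. Adjusted values are 1.739, 1.915, 2.322 and 2.764 at r = 0.3, 0.5, 0.7 and 0.8.

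| assumed d | unadjusted | r = 0.3 | r = 0.5 | r = 0.7 | r = 0.8 |
|---|---|---|---|---|---|
| 0.23 | 0.129 | 0.136 | 0.155 | 0.207 | 0.273 |
| 0.46 | 0.370 | 0.399 | 0.467 | 0.624 | 0.773 |
| 0.65 | 0.633 | 0.673 | 0.756 | 0.896 | 0.969 |
| 0.92 | 0.902 | 0.926 | 0.964 | 0.995 | 1.000 |

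The last row is the difference in change, 4f = 4 × 0.23 = 0.92 SD, implied if 0.23 is f for the interaction.

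**4. Chance imbalance, 26 per arm.** The standardised T0 difference has SD √(2/26) = 0.277, so its 95% range is ±1.96 × 0.277 = ±0.54. The probability that it exceeds 0.3 SD in either direction is 28%; for 0.5 SD it is 7%. Given an imbalance b, the unadjusted T2 difference is shifted by r × b. For b = 0.5 that is 0.15 SD at r = 0.3 and 0.40 SD at r = 0.8. With no true effect, the conditional rejection probability is then about 7% at r = 0.3, 11% at 0.5, 16% at 0.7 and 19% at 0.8. For b = 0.3 it stays between about 3% and 5%. Averaged over all allocations it remains 5%.

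**5. If change scores were meant.** The article does not literally exclude them. With equal variances at T0 and T2, a change score has 2(1 − r) times the T2 variance: 1.40, 1.00, 0.60 and 0.40 at the four values of r. ANCOVA's 0.91, 0.75, 0.51 and 0.36 is smaller each time.

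**The case against.** **It is a choice, not an error.** An unadjusted comparison after simple 1:1 block randomisation is valid, and unstratified allocation is acceptable. This stands. A reader might infer from step 4 that the trial's type I error is inflated; it is not. Only the error conditional on a sizeable imbalance rises.

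**The gain may be small.** At r = 0.3 the variance falls by only 9%, and power at d = 0.46 moves from 37% to 40%. If the effect really is 0.92 SD, the unadjusted test already has 90% power and r = 0.5 lifts it to 96%. This stands, so no single headline gain is supported. In particular, 0.46 is not a figure in the article, and the low absolute power in that row mostly reflects the chosen d.

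**Age is not noise in both primary outcomes.** A reader might infer that it is. The AIMS raw score is converted to a percentile. If that percentile is age-referenced, as Table 2 suggests, most age variation is already removed there. The age argument is therefore mainly about the IMP. The baseline argument applies to every outcome.

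**The plan is not wholly without covariates.** Correct: Intervention promises therapy dose. But that adjusts for neither T0 nor age, and the named tests cannot fit it.

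**Test switching after unblinding.** The choice of test by distribution could be read this way. The article does not support that: Blinding keeps the analyst blind, and Data management stores data without group labels. What remains is a data-dependent choice with no stated rule. Pairing Cohen's d with a rank test is a minor descriptive mismatch.

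**The full analysis plan may say more.** It may, but the article itself names the contrast, the tests and the effect measure, so this is a stated choice rather than an omitted detail.

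**Conclusion.** The point holds as a recommended improvement. The named analysis discards T0 scores that the trial collects for every outcome, and it discards age for an IMP score with no age standardisation described. It is valid under randomisation; the loss is precision and protection against chance imbalance.

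The variance removed lies between 9% and 64% for assumed r from 0.3 to 0.8. The article supplies no standard deviation, no T0-T2 correlation and no metric for 0.23, so neither the variance reduction nor the power gain can be narrowed further from it. The added gain from including age cannot be quantified from the article at all.

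Separately, and without any assumption, the therapy-dose statement under Intervention and the tests under Statistical analysis cannot both be carried out as written.

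**What to change.** Replace the sentence on the effect tests with a prespecified model:

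- **Primary outcomes.** A linear model (ANCOVA) of the T2 score on arm and the same measure's T0 score, with corrected age at T0 added, chiefly for the IMP. Report the adjusted difference and its 95% CI.
- **Secondary outcomes.** The same baseline-adjusted model.
- **Skewed residuals.** Keep the model and use robust or bootstrap standard errors. Keep the Mann-Whitney test as a sensitivity analysis, so that the primary method does not depend on the observed distribution.
- **Therapy dose.** Reconcile Intervention with Statistical analysis by keeping this covariate out of the primary model, because it is measured after randomisation and may itself be affected by the assigned arm.
- **Optional.** A mixed model using T1 and T2 for the IMP and AIMS, with the T2 contrast primary. The article gives T1 the role of checking progress and possibly redirecting activities, so this is not needed to resolve the point.

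The cost is a change of wording made before the data are analysed and one or two degrees of freedom. All variables are already collected, so no new data are needed, and a linear model is standard software. Availability of robust or bootstrap standard errors in the stated software release should be checked.
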